**Figure 1 F1:**
[figure not shown]
**Study Design**.

Initially, patients will undergo a washout period where they receive placebo for 4 weeks after providing informed consent. Following the washout period, eligible patients will be randomized to one of four treatment arms (placebo [A]; linagliptin 5 mg [B]; linagliptin 10 mg [C]; or voglibose 0.6 mg [D]). Patients randomized to Group A will receive a placebo for 12 weeks after which they will receive linagliptin for 40 weeks; patients in the Group B (linagliptin 5 mg) and Group C (linagliptin 10 mg) treatment arms will receive the study drug for up to 52 weeks. Patients randomized to Group D (voglibose 0.6 mg) will receive the treatment for 26 weeks after which they will be switched to linagliptin for 26 weeks (Figure 1). The treatment change to linagliptin in Groups A and D involves an additional patient randomization to either 5 mg or 10 mg, from which data on the long-term safety and tolerability of linagliptin will be collected. The doses of linagliptin used in this study are based on previous reports of DPP-4 activity in Japanese T2DM patients [11].

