### Study Endpoints

The proposed comparison of efficacy between linagliptin (5 and 10 mg) and both placebo and voglibose is based on changes in HbA_1c _levels from baseline at 12 and 26 weeks, respectively. The primary comparison between linagliptin 10 mg and placebo is planned at 12 weeks, and the comparison between linagliptin 10 mg and voglibose 0.6 mg is planned at 26 weeks. To investigate dose-response relationships, a subsequent comparison is made at those time points between linagliptin 5 mg and placebo (12 weeks) and voglibose 0.6 mg (26 weeks).

Other parameters of interest measured will include inhibition of plasma DPP-4 activity, the proinsulin/insulin ratio, the homeostasis model assessment (HOMA) indices for insulin resistance and insulin secretion, body weight, waist circumference and plasma concentrations of linagliptin. Adverse event, safety, laboratory and hematology data will be collected during the study and will form part of the secondary endpoint data for determining the long-term safety profile of linagliptin.

Patient reported outcomes will be assessed using the Diabetes Treatment Satisfaction Questionnaire (DTSQ) modified by Ishii [12], consisting of 6 items assessing treatment satisfaction and 2 items assessing the perceived frequencies of hyperglycaemia and hypoglycaemia.

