### Study Randomization

Four treatment arms are used to investigate the effective dose and safety profile of linagliptin in the study population. Randomization will be based on the Zelen rule [13] and follow a predefined allocation ratio of 2:2:2:1 (linagliptin 5 mg: linagliptin 10 mg: voglibose: placebo). Allocation to treatment groups is balanced for the potentially confounding effects of patient background and baseline characteristics, HbA_1c _(stratified into two categories; < 8.5% and ≥ 8.5%), the number of pre-study use of antidiabetic drugs, gender and study site.

Treatment allocation is conducted by a sponsor-independent contractor. Following informed consent, the investigator completes a registration form that is sent to the allocation center. The registration form includes data on the subjects' inclusion and exclusion criteria. After receiving the registration form, the allocation center sends a registration report to the investigator. The investigator confirms that the patient satisfies the study criteria and sends a second registration form to the allocation center once the 4-week washout period is completed. The allocation center randomizes the patient according to the pre-defined criteria above and this information is provided to the investigator. Randomization is done once at the enrollment of study. At the randomization after the enrollment, patients are assigned, to 6 groups: placebo - linagliptin 5 mg, placebo - linagliptin 10 mg, linagliptin 5 mg, linagliptin 10 mg, voglibose - linagliptin 5 mg, and voglibose - linagliptin 10 mg. Therefore all patients ultimately take either linagliptin 5 mg or 10 mg, unless they withdraw or drop out the study.

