#### Analysis for the primary endpoint

Baseline glycosylated hemoglobin levels and the number of antidiabetic drugs used before study enrollment are included in the model as covariates.

Changes in HbA_1c _level from baseline to 12 weeks of linagliptin treatment are analyzed in accordance with the model below, in order to compare with placebo in the double-blind treatment phase:

Where:

*y*_*ijk *_: change in HbA_1c _at 12 weeks from baseline

*BHbA1c*_*i *_: HbA_1c _of i-th patient at baseline (i = 1, 2,..., n)

*Dose*_*j *_: j-th dose group (j = 0: placebo, 1: 5 mg, 2: 10 mg)

*Diabtreat*_*k *_: number of previously used antidiabetic drugs (k = 0: no treatment, 1: one antidiabetic drug, 2: two antidiabetic drugs)

Comparisons conducted at 12 weeks are between linagliptin and placebo. Patients who received placebo for 12 weeks and are then randomized to receive either linagliptin 5 mg or 10 mg are excluded from this analysis. Values of HbA_1c _following treatment with linagliptin are to be compared with those for voglibose after 26 weeks if linagliptin treatment fails to achieve a statistically significant difference in HbA_1c _levels relative to placebo (primary comparison dose at 12 weeks). The dosing schedule for linagliptin increases from 5 mg to 10 mg during study if linagliptin 5 mg fails to demonstrate superiority to placebo at 12 weeks. In addition, the study stops if neither of the linagliptin arms shows statistically significant differences from placebo in HbA_1c _levels at 12 weeks.

The model for HbA_1c _at 26 weeks is:

Where:

*y*_*ijk *_: Change in HbA_1c _at 26 weeks from baseline

*HbA1c*_*i *_: HbA_1c _of i-th patient at baseline (i = 1, 2,..., m)

*Drug*_*j*_: j-th treatment group (j = 1:5 mg, 2:10 mg, 3:voglibose)

*Diabtreat*_*k *_: number of previously used antidiabetic drugs (k = 0:no treatment, 1:one antidiabetic drug, 2:two antidiabetic drugs)

Comparisons for HbA_1c _between groups are performed weekly by the closed testing procedure [15]. No formal analysis will be performed for safety and tolerability data collected during the three stages of the study. Data will be summarized in terms of treatment received.

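### A conditional rule raising 5 mg to 10 mg after week 12 conflicts with the fixed 5 mg sequence and, if it fires, leaves the 26-week 5 mg level partly describing another regimen

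*Protocol article*

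**What the plan says.** All places are in the protocol article.

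- **Dose rule, acting on the week-12 test** (Analysis for the primary endpoint): "The dosing schedule for linagliptin increases from 5 mg to 10 mg during study if linagliptin 5 mg fails to demonstrate superiority to placebo".
- **Stopping rule** (same paragraph): "the study stops if neither of the linagliptin arms shows statistically significant differences from placebo" at 12 weeks. One dose succeeding is therefore enough for the study to continue.
- **Treatment of Groups B and C** (Study Stages, text under Figure 1): these "treatment arms will receive the study drug for up to 52 weeks". A treatment change is described only for Groups A and D.
- **Randomization** (Study Randomization): "Randomization is done once at the enrollment of study", to six sequences. One is linagliptin 5 mg with no switch. None is 5 mg followed by 10 mg.
- **26-week comparison** (Study Endpoints): to study dose-response, "a subsequent comparison is made at those time points between linagliptin 5 mg and placebo (12 weeks) and voglibose 0.6 mg (26 weeks").
- **26-week model** (Analysis for the primary endpoint): the treatment factor is "j-th treatment group (j = 1:5 mg, 2:10 mg, 3:voglibose"), with no level for a raised dose.
- **Power at 26 weeks** (Sample size): based on 26 weeks of 5 mg, a 0.7% change against 0.25% for voglibose.
- **Analysis principle** (Statistical analysis): intention to treat, on the full analysis set.

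**The concern.** The article gives two dosing schedules for the 5 mg arm. One is fixed at randomization. The other changes on a group-level test at week 12. The analysis sections follow only the first.

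The rule has a live path: 5 mg fails against placebo, 10 mg succeeds, the study goes on and the 5 mg dose rises. On that path a patient keeps the label 5 mg under intention to treat while possibly taking 10 mg before the week-26 measurement. The Background section says up to 12 weeks of exposure shows a drug's full effect on HbA1c, so a switch soon after week 12 could largely determine the week-26 value.

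At stake are the 26-week estimate for 5 mg against voglibose, the dose-response reading that this comparison is meant to serve, and the amount of long-term exposure on 5 mg.

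**Working it through.** **1. The plan's own figures.** From Sample size: one-sided 2.5%. At week 12 the difference is 0.5% and the SD 0.9%, with 52 and 104 patients. At week 26 the difference is 0.45% and the SD 1.0%, with 105 per group.

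- Week 12: SE = 0.9 × √(1/52 + 1/104) = 0.153; 0.5/0.153 = 3.27; power = Φ(3.27 − 1.96) = 90.5% (90.2% by noncentral t).
- Week 26: SE = 1.0 × √(2/105) = 0.138; 0.45/0.138 = 3.26; power = Φ(3.26 − 1.96) = 90.3% (90.1% by noncentral t).
- Dropout of 15%: 52/0.85 gives 62, 104/0.85 gives 123 and 105/0.85 gives 124, against stated targets of 63 and 126. The total 63 + 3 × 126 = 441 agrees.

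The sample sizes reproduce and are not in dispute.

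**2. Chance that 5 mg fails at week 12.** This is 1 − power (noncentral t). The 52/104 column uses the numbers after dropout; 63/126 uses the recruitment targets. Effects below 0.5% are assumptions.

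| True 5 mg effect | 52/104 | 63/126 |
|---|---|---|
| 0.5% (plan) | 9.8% | 5.2% |
| 0.4% | 26.1% | 18.3% |
| 0.3% | 50.4% | 42.5% |

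**3. Chance that 5 mg fails and the study continues.** This needs an effect for 10 mg, which the article does not give. Simulation of 1,000,000 trials with a shared placebo arm, SD 0.9% and critical value 1.96:

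| Assumed 5 mg / 10 mg effect | 5 mg fails, 10 mg succeeds: 52/104 | 63/126 |
|---|---|---|
| 0.5% / 0.5% | 5.3% | 3.2% |
| 0.5% / 0.6% | 8.0% | 4.5% |
| 0.3% / 0.5% | 41.1% | 37.3% |

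In the first row both doses fail, and the study stops, in a further 4.1% and 1.8%.

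**4. How much of the arm would be affected.** Assume that the test waits for the last patient's week-12 value and that the change is immediate. A patient randomized w weeks before the last one is then at week 12 + w, with max(0, 14 − w) weeks on the raised dose before week 26. Only the last patients approach 14 weeks; anyone randomized more than 14 weeks earlier is unaffected. With even entry over R weeks (R is not given), the affected share is 14/R: all if R ≤ 14, 50% if R = 28, 25% if R = 56.

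**5. What the 5 mg label would then estimate.** For illustration, assume 26-week differences from voglibose of 0.20% on 5 mg and 0.45% for patients raised to 10 mg. With share f switched, the arm estimates (1 − f) × 0.20 + f × 0.45.

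| f | Expected difference | Chance of significance, 105 per group |
|---|---|---|
| 0% | 0.20% | 30% |
| 25% | 0.263% | 47% |
| 50% | 0.325% | 65% |
| 100% | 0.45% | 90% |

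This gives every switched patient the full higher effect, so it is an upper bound on the shift for these assumed effects. The chances of significance are not conditioned on 5 mg having failed at week 12.

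**The case against.** The strongest reply has four parts.

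- **The rule is conditional.** If 5 mg beats placebo at week 12, the 26-week comparison is exactly what the plan says. This stands. A reader might infer that the 26-week result is never one of 5 mg; the text does not support that.
- **No false efficacy claim for 5 mg follows.** The Discussion requires superiority to placebo and voglibose together, and the rule acts only after 5 mg has failed against placebo. The primary comparisons use 10 mg, and Group C's dose is not changed. This also stands.
- **Safety is summarized by treatment received.** That covers how exposure after a change is described. It does not restore long-term exposure on 5 mg.
- **A conditional exception need not contradict a randomization list.** Study Stages says study drug, not assigned dose, and the rule names the linagliptin schedule rather than Group B, so it might also cover later 5 mg use in Groups A and D. This stands in part: the scope is unclear. But no section says that the six sequences admit an exception, and the 26-week model has no level for one. The sentence before the rule, which ties the voglibose comparison to a failure against placebo, makes it less clear what follows such a failure.

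A reader might also infer that acting on the week-12 result breaks the blind. The article does not say who sees that result or how a change would be supplied. A condensed article commonly leaves this to the full protocol, so loss of blinding is not shown.

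**Conclusion.** The point holds in conditional form. The sections give incompatible schedules for the 5 mg arm. If the rule fires and 10 mg succeeds, following the analysis as written may report an arm partly on 10 mg as 5 mg. The harm is limited to the 26-week 5 mg estimate, the dose-response reading and the long-term 5 mg exposure data.

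The trigger has a probability of about 5% to 10% at the planning assumptions for 5 mg. The branch in which the study continues has about 3% to 5%, if 10 mg also has a 0.5% effect. With true effects of 0.3% and 0.5% the latter is 37% to 41%, so the rule is likelier to act when the doses differ, which is when dose-response matters most. The size of the mixture cannot be derived, because recruitment timing is not given.

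**What to change.** Reconcile the dose rule in Analysis for the primary endpoint with Study Stages, Study Endpoints and Study Randomization, and state which patients the rule covers. No view is taken here on which dosing rule applies.

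If a dose change is kept, add one reporting rule. The 26-week comparison for Drug j = 1 is reported as 5 mg only if Group B stayed on its assigned dose through week 26. Otherwise it is labelled 5 mg then 10 mg and is not used for the 5 mg dose-response conclusion.

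The cost is wording in the protocol and analysis plan; no extra patients or visits.

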### Sample size

Sample size calculations are performed using nQuery Advisor^® ^6.0 (Statistical Solutions Ltd, Ireland) software on a Windows-based personal computer. On the basis of clinical studies conducted in Japan and other countries, it is estimated that the overall mean change in HbA_1c _levels after treatment with linagliptin 5 mg QD for 12 weeks will be approximately 0.5% compared with 0% in placebo. This will provide an overall mean between-groups treatment difference of 0.5%. Experience also suggests that the standard deviation of this difference will be approximately 0.9%. Employing an accepted one-sided statistical significance threshold of 2.5% and taking into account the weighting for placebo and linagliptin group randomization ratios (1:2), it is possible to predict a 90% power for the study with sample sizes of no less than 52 patients in the placebo group and no less than 104 patients in the linagliptin groups.

Assuming that HbA_1c _levels for the linagliptin treatment groups will continue to fall with ongoing therapy, estimates suggest that the mean change in HbA_1c _levels from baseline after a 26 week treatment with linagliptin 5 mg, will be approximately 0.7%, compared with 0.25% for voglibose 0.6 mg. It is expected that this difference between treatments will be reflected in a mean difference in HbA_1c _levels from baseline of 0.45% [16]. With a standard deviation of the difference at 1.0% and the level of significance set at 2.5% (one-sided analysis), sample sizes of 105 or more in each group provide a power greater than 90%.

Experience derived from previous clinical trials in patients with T2DM suggests that a discontinuation/dropout rate of approximately 15% can be expected during the current 52-week trial. Assuming that the present study will experience a similar level of subject discontinuation, it is possible to adjust the recruitment targets to maintain study power in anticipation of similar attrition levels. A target sample size of 63 patients in the placebo group and 126 patients each in the linagliptin and voglibose treatment groups (a total of 441 patients overall) is therefore required to power this study appropriately to achieve its primary objectives.

The sample size in the linagliptin group also appears to satisfy the requirements for evaluation of safety in the clinical development of new drugs expected for long-term use in non-fatal diseases [17].

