The study design was selected to reduce the number of patients required to undergo a prolonged placebo exposure by employing an imbalanced randomization (placebo:linagliptin 5 mg:linagliptin 10 mg:voglibose = 1:2:2:2). Using this biased treatment allocation approach, it is possible to minimize the potentially unethical exposure of patients to placebo while maintaining sufficient power to complete the primary statistical comparison. Data after 16 weeks of placebo treatment can be useful for determining a true baseline (treatment naïvety) because any underlying glycemic controlling effects of prior antidiabetic treatment should have had sufficient time to reverse. The 16 week data for glycosylated HbA_1c _levels in the placebo group will not be included in any comparison, but instead will be viewed as an indication of the study population's baseline HbA_1c _values in the absence of the potentially confounding residual effects of previous therapies. A similar number of patients are needed to demonstrate the non-inferiority or superiority of linagliptin to placebo under imbalanced randomization and to voglibose. The study design can also be sufficiently powered for detecting statistically significant differences between linagliptin and placebo or voglibose. Using the methods described, we have calculated that this can be achieved without markedly increasing the number of subjects needed.

The efficacy of short term linagliptin treatment in Japanese T2DM patients was reported by Kanada et al [11]. We set the one-sided hypotheses (2.5% statistically significant level) in the present study as the efficacy of linagliptin is expected to show significant superiority to placebo or voglibose. The efficacy of linagliptin is established only in the case that linagliptin shows superiority to placebo and voglibose simultaneously. Therefore, adjustment for multiple hypotheses is not carried out.

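### The 90% power figures are for each pairwise test alone; for the trial's own criterion (superiority to placebo and to voglibose) one dose has about 83–84% after the planned 15% loss

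*Protocol article*

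**What the plan says.** The Sample size section makes two separate calculations.

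- **Week 12, linagliptin against placebo.** The assumed difference is 0.5% with SD 0.9%, at one-sided 2.5% and 1:2 allocation. With 104 on linagliptin, the article says "it is possible to predict a 90% power for the study with sample sizes of no less than 52 patients in the placebo group".
- **Week 26, linagliptin against voglibose.** The assumed difference is 0.45% with SD 1.0%, again with "the level of significance set at 2.5% (one-sided analysis"). It concludes that "sample sizes of 105 or more in each group provide a power greater than 90" per cent.

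It then allows for about 15% discontinuation over 52 weeks and reaches 63 on placebo and 126 in each other arm, 441 in all. This total "is therefore required to power this study appropriately to achieve its primary objectives".

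The Discussion sets the criterion: "The efficacy of linagliptin is established only in the case that linagliptin shows superiority to placebo and voglibose simultaneously". It gives this as the reason for not adjusting for multiple hypotheses.

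Both sizing effects are those expected for linagliptin 5 mg. Under Study Endpoints, however, "The primary comparison between linagliptin 10 mg and placebo is planned at 12 weeks"; 10 mg is likewise compared with voglibose at 26 weeks, and the 5 mg comparisons follow.

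**The concern.** When two tests must both succeed, no alpha adjustment is needed between them, but the chance of succeeding on both is lower than on either one. The article takes the first consequence and does not mention the second. It describes the 90% from the week-12 calculation as power for the study, and ties the total of 441 to the primary objectives in the plural. A reader would conclude that the risk of missing the trial's efficacy criterion, if the planning assumptions hold, is about 10%. After the planned attrition it is about 16–17%.

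A second gap bears on how the figure may be used. The effects belong to 5 mg, the primary dose is 10 mg, and no effect is stated for 10 mg.

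**Working it through.** **Inputs (Sample size section).** One-sided α = 0.025, so z = 1.960. Week 12: difference 0.5, SD 0.9, n = 52 and 104. Week 26: difference 0.45, SD 1.0, n = 105 per group. Enrolment 63 and 126; loss 15%. Not given: the within-patient correlation ρ between the week-12 and week-26 changes. It is varied from 0 to 0.95.

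**1. Reproduce the pairwise figures.** Power = Φ(δ / SE − 1.960), with SE = SD × √(1/n₁ + 1/n₂).

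- Week 12: SE = 0.9 × √(1/52 + 1/104) = 0.1529; 0.5 / 0.1529 = 3.271; power = Φ(1.311) = 90.5% (noncentral t: 90.2%).
- Week 26: SE = 1.0 × √(2/105) = 0.1380; 0.45 / 0.1380 = 3.261; power = Φ(1.301) = 90.3% (noncentral t: 90.1%).
- Enrolment: 52 / 0.85 = 61.2 and 105 / 0.85 = 123.5, so at least 62 and 124. The stated 63 and 126 cover this, and 63 + 3 × 126 = 441.

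The stated figures are confirmed.

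**2. Correlation of the two test statistics.** The two tests of one dose share only that linagliptin arm, of size n. Placebo has n/2 and voglibose has n.

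- Covariance of the two differences: ρ × SD₁ × SD₂ / n.
- Variances: 3 × SD₁² / n and 2 × SD₂² / n.
- Correlation: ρ / √6, so at most 0.41.

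The unknown ρ therefore has limited influence.

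**3. Joint power for one dose.** This is the bivariate normal probability that both statistics exceed 1.960, at the stated 5 mg effects.

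| Patients analysed | Power, week 12 | Power, week 26 | Joint power, ρ from 0 to 0.95 |
|---|---|---|---|
| Minimum: 52 placebo, 104 linagliptin, 105 voglibose | 90.5% | 90.2% | 81.6–83.2% |
| 15% loss: 53.55 and 107.1 | 91.3% | 90.9% | 83.0–84.4% |
| Assumed 5% loss at week 12 and 10% at week 26: 60 and 120; 113 and 113 | 94.0% | 92.3% | about 87–88% |
| No loss: 63 and 126 | 95.0% | 94.6% | 89.9–90.6% |

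At ρ = 0 the joint value is the product: 0.905 × 0.902 = 0.816 in the first row, and 0.913 × 0.909 = 0.830 in the second. In the first row the week-26 test uses 104 against 105; using 105 in both groups raises the joint figures by about 0.1 point.

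**The case against.** **No joint 90% is claimed.** Each percentage follows a single comparison, each is right, and the sentence about 441 patients contains no percentage. The Discussion also speaks of power to detect differences from one comparator or the other. It is true that this is not an arithmetic error. But calling the first figure power for the study, and saying that the total serves the primary objectives, attaches it to a goal that the Discussion defines as winning both tests.

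**The shortfall depends on attrition.** The 15% is a 52-week rate, whereas the tests are at weeks 12 and 26 on an intention-to-treat full analysis set. This stands: smaller losses raise joint power towards 90%. However, the plan added the extra patients to preserve power after a 15% loss, so its own power statement refers to the numbers left after that loss.

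**The figure is not established for 10 mg.** This also stands. As an illustration only, suppose 10 mg changes 10% larger: 0.55 and 0.77, so differences of 0.55 from placebo and 0.77 − 0.25 = 0.52 from voglibose. Joint power after 15% loss would then be about 93% at ρ = 0.7. A smaller effect would lower it.

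**A stronger reading that the documents do not support.** A reader might infer that 5 mg, tested after 10 mg, has only about 71–75% power, because all four tests must succeed. That needs equal effects for both doses and a strict gate in which 10 mg wins both its tests before 5 mg can succeed. Study Endpoints only calls the 5 mg comparison subsequent. The primary-endpoint analysis section names closed testing without giving a hierarchy, and its stopping rule requires both doses to fail against placebo. The Discussion's criterion names no dose. If either dose sufficed, power after 15% loss would be about 93–94% with equal effects.

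**Conclusion.** The point holds for one dose against both comparators. The plan's 90% and over 90% are pairwise. For the criterion in the Discussion, power is about 82–83% at the minimum numbers and about 83–84% after the planned 15% loss. It rises to about 87% under the assumed 5% and 10% losses and to about 90% with none.

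These figures rest on the stated effects, SDs and one-sided level, on a normal approximation (the noncentral t lowers each pairwise figure at the minimum numbers by about 0.3 point), and on ρ between 0 and 0.95, which moves the result by less than 2 points. They apply to 5 mg as sized, and to 10 mg only if its effects are assumed equal.

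This is a misdescribed power. The pairwise calculations, the total of 441 and the type I error control across the two comparators are not in question.

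**What to change.** Keep 441 patients and revise the text of the Sample size section and the Discussion:

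1. State that about 90% is the power of each comparison taken separately.
2. Report the joint power (placebo at week 12 and voglibose at week 26) for one dose as about 83–84% after 15% attrition, name that loss assumption, and preferably show the range up to about 90% with no loss.
3. State that the sizing effects are those given for 5 mg while 10 mg is the primary dose. Either say that equal effects are assumed or give the effects expected for 10 mg.
4. Qualify the statements that the study is appropriately or adequately powered to match.
5. Leave out a four-test figure for 5 mg, or give it only as conditional on equal effects and a strict gate by 10 mg.

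The cost is wording only: no change to enrolment, analysis or alpha, but a less favourable stated power. If the sponsor preferred 90% joint power after 15% loss, about 63–64 evaluable on placebo and 126–128 in each other arm would be needed, which means enrolling about 75–76 and 149–151. That is 75 + 3 × 149 = 522 to 76 + 3 × 151 = 529 patients instead of 441.
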